### Hypothesis

GBS patients with the poorest prognosis (mEGOS 6-12) may benefit from a second course of IVIg when administered within the first weeks after onset of disease, when nerve damage is most likely still reversible.

## 2. OBJECTIVES

### Primary objective

To determine whether a second IVIg dosage in GBS patients with a poor prognosis improve functional outcome after 4 weeks.

### Secondary objectives

To investigate whether:

- a second IVIg dosage in GBS patients with a poor prognosis improve functional outcome or muscle strength after 8, 12 and 26 weeks.
- a second IVIg dosage in GBS patients with a poor prognosis lowers the percentage of patients needing artificial ventilation, lower the time (number of days) on respirator or time on the intensive care.
- a second IVIg dosage in GBS patients with a poor prognosis reduces the time to hospital discharge.
- a second IVIg dosage in GBS patients with a poor prognosis reduce the chance of secondary deterioration due to treatment-related fluctuations (TRF†).
- patients treated with a second IVIg dosage develop more complications possibly related to the second IVIg treatment.
- a second IVIg dosage in GBS patients with a poor prognosis lowers the percentage of patients that die because of GBS.
- the serum IgG increase after the first IVIg dosage is lower in patients with a poor prognosis.
- serum IgG increases further (and to what extent) after administration of a second IVIg dosage.

† A TRF is defined as (1) improvement in the GBS disability score of at least one grade or improvement in the MRC sum score (0-60) of more than 5 points after completion of therapy, followed by a worsening in the GBS disability score of at least one grade or a decrease in the MRC sumscore of more than 5 points within the first months after onset of disease or (2) stabilization of the clinical course for more than 1 week after completion of therapy, followed by a worsening of at least one grade of the GBS disability score or more than 5 points on the MRC sumscore.

### 3. STUDY DESIGN

A double-blind randomized placebo-controlled trial design will be used in selected patients with a poor prognosis. In patients with a good prognosis the study will have an observational design.

- All GBS patients in need of IVIg treatment, according to the treating neurologist, in a standard dosage of 2 g/kg in 2-5 consecutive days are potentially eligible for this study after obtaining informed consent.
- When patients sign 'Informed consent' they principally agree to be randomized to get a second IVIg dose or placebo when having a poor prognosis at day 7 and to be followed up for 6 months.
- Patients with the poorest prognosis based upon the modified EGOS (mEGOS 6-12) after the first IVIg course will be randomized to get a second course of IVIg (Nanogam®) in a dosage of 8 ml/kg (=0,4 g/kg) for 5 days or placebo (GPO®) in a dosage of 8 ml/kg for 5 days in a blinded fashion.
- mEGOS must preferentially be assessed 7 days after start of first IVIg course, with a range to 8 or 9 days. Trial medication needs then to be started within 24 hours when indicated according to the mEGOS score (see figure 4).
- Patient follow-up will be 6 months.
- Total patient inclusion will end when 44 patients with a poor prognosis received a second IVIg dosage.
- After covariate adjustment, to deal with variation between patients in baseline risk and to increase statistical power, data of the placebo group and the intervention group will be compared.

This is shown in the flowchart (table 2).

[figure not shown]

#### Inclusion procedure

We contacted neurologists of 93 hospitals in the Netherlands by information letter. We also will contact neurologists formally being member of the Dutch GBS study group, additionally this study will be brought under the attention during national meetings of neurologists. When neurologists are willing to cooperate in this study local feasibility in their hospital will be checked according to GCP guidelines and neurologists will be

provided with pocket size inclusion cards. These cards describe in – and exclusion criteria, checklists for the trial procedures and additional contact information.

When a GBS patient in need of IVIg treatment is admitted in one of the cooperating hospitals and in –and exclusion criteria are met the patient (or his / her legal representative) is asked to participate in this study.

### **Data collection**

1. Questionnaires encompassing patient demographics, preceding events, indicators of disease severity, disease progression and outcome will be filled out at predefined standard time points by the PI and after monitoring will be send to the coordinating center at Erasmus MC.
2. Blood samples, CSF and a throat swap will be send to the coordinating center. The specimen will be analyzed at the Erasmus MC at the department of neuro-immunology and microbiology. In addition DNA will be stored for future gene polymorphism studies. We expect that the collected samples will be of interest for future research in the next decade, so we will store the material for 15 years, when informed consent is obtained.
3. An EMG is performed in the standard work-up of GBS patients. The PI will be asked to perform an EMG following predefined guidelines to enable classification of electrophysiological data according to Hadden[28] as indicative of primary demyelinating disease, equivocal, primary axonal, unexcitable and normal. Guidelines were developed in collaboration with the clinical neurophysiology department of the Erasmus MC.
4. After discharge from the hospital, patients will be asked to visit the outpatient clinic of the local hospital for follow-up. When a patient is fully recovered according to the GBS disability score, the MRC sum score and the ONLS score at 3 months, they will be discharged from further follow-up, presuming GBS is a monophasic disease.
5. Patients of 18 years or older included in hospitals in Rotterdam, will be asked to have a skin biopsy (3 mm punch) to determine intraepidermal nerve fibre (IENF) density. Yet, unpublished research from our group showed prognostic value of IENF density in skin biopsies. We aim to expand this study. Skin biopsy for determination of IENF density is a standard - minimal invasive - procedure requiring local anesthetics and resulting in a small scar. Estimated time 10 minutes. The skin biopsy protocol includes a skin biopsy at the distal leg and a lumbar paraspinal biopsy. The biopsies will be taken in the first week of admission and after 6 months. Skin biopsies are additional to the standard protocol, patients can decide to participate in the SID-GBS study without giving approval for taking skin biopsies. Therefore patient information and informed consent forms are strictly separate.

Further follow-up is requested from all patients in the informed consent letter to enable further studies involving long-term outcome. Improvement of neurological deficit is known to occur until many years after onset of GBS[29], especially in severely affected patients. Long-term follow-up (at 1 or 2 years) will be executed by semi-standardized telephone interviews.

Table 2; flowchart

[figure not shown]

## **4. STUDY POPULATION**

### **4.1. Population (base)**

This study will be executed in the Netherlands. The annual incidence of GBS in the Netherlands is 1.2 per 100.000 persons [2], so there will be around 200 newly diagnosed GBS patients each year. At present 67 hospitals in the Netherlands are willing to participate in this study.

The inclusion period will start around October 2009 and is expected to end 3 years later. In this period we expect to include the needed 174 patients, of which 50% (87 patients) will be randomized to receive a second dosage of Nanogam® or placebo.

### **4.2. Inclusion criteria**

#### **A. To enter this GBS study**

- Patients are diagnosed with GBS[30].
- There is an indication to start IVIg (irrespective of co-treatment with methylprednisolon (MP)) therapy:
  1. Patient is unable to walk unaided for >10 meter (grade 3, 4 or 5 of the GBS disability scale)
  - or
  2. There is otherwise an indication to start IVIg (with or without MP) treatment according to the treating neurologist.
- Onset of weakness due to GBS is less than 2 weeks ago.
- Signed informed consent.

#### **B. To be randomized in the second IVIg dose phase (RCT), patients must fulfill the following criteria:**

- First IVIg (with or without MP) treatment with Nanogam® started within 2 weeks from onset of weakness.
- IVIg treatment has been 2g/kg administered in 2-5 days.
- Poor prognosis based upon the modified EGOS (mEGOS 6-12) at day 7 after start of first IVIg treatment.

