### **Rationale for the study**

There are several arguments suggesting that a second IVIg course can be effective in patients with a poor prognosis;

1. It is known that about 10% of GBS patients only have short-lasting improvement after a single IVIg course ('treatment-related clinical fluctuation'), a second dose of IVIg is then followed by functional improvement, suggesting that one IVIg course in these patients is insufficient [17]
2. A second course of IVIg is suggested to be effective in a small uncontrolled series of severe unresponsive GBS patients[18]

3. Additionally, recent data from our group show that patients with a relatively minor increase in serum IgG level after IVIg treatment recover significantly slower and fewer patients were able to walk unaided after 6 months (Kuitwaard, Ann Neurol in press).

Based on these findings, it is likely that at least a proportion of GBS patients may benefit from repeated courses of IVIg [6], especially the subgroup of patients with poor prognosis.

There are several arguments, however, for not treating all patients with a second IVIg course;

1. A proportion of GBS patients recover relatively well with the current treatment regime.
2. Thrombo-embolic (TE) complications are rare but are regularly described with the use of IVIg, most likely because of a rise in plasma viscosity [19-25]. A recent case-control study found that the risk of TE complications was elevated in patients with multiple cardiovascular risk factors[26]. Neurologic patients may be more prone to this complication because of their impaired mobility [20].
3. Presently the consumption of IVIg is increasing at an annual rate of 5% in Europe and 11% in the USA. A relative shortage of IVIg has been witnessed in recent years. In addition, IVIg is used in an off-label manner for nearly 100 conditions. High costs and limited resources will require targeted use of IVIg[21, 27].

We think it is justified to treat GBS patients with high risk of poor outcome with a second IVIg course because in those patients the benefits outweigh the risks.

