## 7.2. Randomization, blinding and treatment allocation

All GBS patients in need of IVIg treatment are potentially eligible for this study. All participants will be evaluated after first IVIg treatment and scored following the modified EGOS model. Patients with a poor prognosis according to this model will be randomized to receive a second IVIg dosage or placebo. For that a randomization website is used (see the signed agreement with CTCM). A computer-generated list of random assignments (block randomization per site) is prepared in advance. When a PI registers a patient to the website a box number is generated and an email with this box number will be sent automatically to the local pharmacist (and the central pharmacy of the Erasmus MC, the coordinating investigator, the co-investigator, Sanquin and the registering PI). The box number corresponds to the randomization list and the local pharmacist will prepare the study medication according to the randomization allocation. The PI will prescribe the trial medication in the same dosage as the first treatment (2 g/kg administered in 5 consecutive days). The coordinating investigator, the co-investigator, the PI and the trial coordinator of Sanquin as well as the patient will be blinded to the treatment.

Blinding will be broken in case of a Serious Adverse Event considering the severity of the adverse event and the likeliness of a relation to IVIg treatment after conference between the investigators, Sanquin and the treating neurologist. The treating neurologist will then be unblinded and is responsible for treatment of the possible side effects of the IVIg treatment.

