Blinding will not be broken in case of a TRF, a TRF is defined as (1) improvement in the GBS disability score of at least one grade or improvement in the MRC sum score (0-60) of more than 5 points after completion of the first IVIg course, followed by a worsening in the GBS disability score of at least one grade or a decrease in the MRC sumscore of more than 5 points within the first months after onset of disease or (2) stabilization of the clinical course for more than 1 week after completion of the first IVIg course, followed by a worsening of at least one grade of the GBS disability score or more than 5 points on the MRC sumscore. When a TRF occurs during the trial medication course, the trial medication will be stopped and an open IVIg course will be started, as this is standard treatment for a TRF. This decision should always be taken after consultation with the trial coordination.

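### No visible rule covers a treatment-related fluctuation between the end of the first IVIg course and the first trial infusion, and the TRF definition starts its clock before randomisation

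*Protocol*

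**What the plan says.** **Entry to the randomised phase.** Section 4.2B sets three conditions: the timing of the first course, its total dose and duration, and "Poor prognosis based upon the modified EGOS (mEGOS 6-12) at day 7 after start of first IVIg treatment". Section 7.2 repeats the rule without exception: "Patients with a poor prognosis according to this model will be randomized to receive a second IVIg dosage or placebo". TRF appears neither in Section 4.2B nor in the exclusions and relative contra-indications of Section 4.3.

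**Timing.** The first course lasts 2 to 5 days (Section 4.2B). The mEGOS is scored on day 7, or at the latest day 8 or 9, and "Trial medication needs then to be started within 24 hours when indicated according to the mEGOS score" (Section 3).

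**Definition of TRF.** Section 7.2 has two limbs. The first is a gain of at least one disability grade, or "improvement in the MRC sum score (0-60) of more than 5 points after completion of the first IVIg course", followed by a loss of similar size. The second is "stabilization of the clinical course for more than 1 week after completion of the first IVIg course", followed by such a loss. Both run from the end of the first course.

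**Management of TRF.** Section 7.2 states: "When a TRF occurs during the trial medication course, the trial medication will be stopped and an open IVIg course will be started". The reason given is general: "as this is standard treatment for a TRF". Section 1 (Rationale for the study) says of patients with a TRF that "a second dose of IVIg is then followed by functional improvement, suggesting that one IVIg course in these patients is insufficient".

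**Endpoint.** The percentage of patients with a TRF is a secondary endpoint (Section 7.1.2). The footnote to Section 2 dates a TRF from the end of therapy without saying which course is meant.

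**The concern.** The TRF definition reaches back to a period before any trial infusion, whereas the TRF instruction begins only with trial medication. An event in between is a TRF by the protocol's own definition and has what the protocol calls a standard treatment, yet the entry rules send the patient to randomisation with a one-in-two chance of placebo. The same event a day later, with trial medication running, leads to open IVIg.

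Two things are at stake. Investigators have no common instruction for this interval, so sites may act differently. In addition, a TRF that happened before allocation could be counted as an outcome of allocation.

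**Working it through.** The protocol states no figure for TRFs in this interval, so there is none to reproduce. The denominator does reproduce from Section 4.4: 0.60 × 290 = 174 patients, and 0.50 × 174 = 87 randomised.

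1. **Length of the interval.** Take the day of the first infusion as day 0. The last infusion falls on day (course length − 1), which is day 1 for a 2-day course and day 4 for a 5-day course. The first trial infusion falls between day 7 and day 9 + 1 = 10.
   - 5-day course: 7 − 4 = 3 to 10 − 4 = 6 days.
   - 2-day course: 7 − 1 = 6 to 10 − 1 = 9 days.
   - Overall: 3 to 9 days. If the first infusion is called day 1, each figure is one day shorter.

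2. **Which limb can be met.** The first limb (improvement, then worsening) has no minimum duration and can be met anywhere in the interval. The second needs more than 7 days of stability. After a 5-day course the longest interval is 6 days, so it cannot be met. After a 2-day course it fits only when the interval reaches 8 or 9 days, that is, with late scoring. In practice only the first limb applies.

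3. **Whether mEGOS screens these patients out.** It does not. By Table 1, any MRC sumscore of 40 or less scores at least 6, whatever the path to it.
   - Worsening can create eligibility. At age 50 without diarrhoea, MRC 45 scores 1 + 3 = 4, and MRC 39 scores 1 + 6 = 7.
   - It need not. A fall from 28 to 20 stays in one band. A fall from 56 to 48 reaches 6 only with age over 60 and diarrhoea (3 + 2 + 1). Worsening after the score is taken cannot change it.

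4. **Sections 4.2B and 7.2 side by side, for a patient with mEGOS 6-12.**
   - TRF before the first trial infusion: Sections 4.2B and 7.2 randomise, and no TRF instruction applies.
   - TRF during trial medication: Section 7.2 stops it and starts open IVIg, after consultation with the trial coordination.

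5. **Number affected.** Section 1 gives about 10% TRF among GBS patients in general, at any time. If that held in the randomised group, 0.10 × 87 = 8.7 patients would have a TRF at some point. The share f falling in the interval is not given. An assumed f of 2% gives 8.7 × 0.02 = 0.2 patients, and an assumed f of 30% gives 8.7 × 0.30 = 2.6. The answer is set by the assumption, so this range is not an estimate.

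6. **Effect on the TRF endpoint.** Let q be the share with a TRF before randomisation, equal in both arms in expectation. Let p₁ and p₀ be the later TRF risks in the remaining patients on IVIg and placebo. Counting each patient once, the percentages are q + (1 − q)p₁ and q + (1 − q)p₀. Their difference is (1 − q)(p₁ − p₀), which shrinks towards zero but does not move in favour of either arm. With q = 0.10 × f and the same assumed f, q runs from 0.2% to 3%, so 99.8% to 97% of the difference is kept.

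**The case against.** The strongest reply is that this is a silence and not a contradiction, and that is correct. A reader might infer that the protocol gives two opposing rules for the same event. It does not: Section 4.2B never mentions TRF, and Section 7.2 limits its instruction to the time when trial medication is being given. The tension is between the general reason in Section 7.2 and an entry rule that takes no account of it.

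A reader might also infer that a patient already given an open second course could then be randomised, so that the IVIg arm would receive a third course. The documents do not support this. Section 4.2B requires that IVIg treatment has been 2 g/kg over 2 to 5 days, and its natural reading excludes someone who has had more.

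Nor can a probability be attached to at least one such patient arising. The 10% is for GBS patients in general, and its timing is not given.

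Three further replies carry some weight. The investigator may withdraw a patient for urgent medical reasons (Section 7.4), but that is a general safeguard and not a rule for TRF. The flowchart (Table 2) and Figure 4 are not shown and could address the step. The counting window of a secondary endpoint is often left to the statistical analysis plan. Here, however, the protocol itself fixes a start for the TRF clock in Section 7.2, and that start precedes allocation.

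**Conclusion.** The point holds as a minor one. On the visible text, a TRF between the end of the first course and the first trial infusion is counted as a TRF by Section 7.2 but managed by no rule, and the entry criteria would randomise the patient if mEGOS is 6-12. That sits badly with the protocol's own statement about how a TRF is treated. This review does not say which clinical rule is right.

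The interval is about 3 to 9 days, and essentially only improvement followed by worsening can qualify in it, so few patients are likely to be affected. Counting pre-randomisation events would weaken the secondary TRF comparison slightly and would not bias it. The definition of the primary endpoint does not depend on TRF. The conclusion assumes that the figures not shown contain no rule for this interval.

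**What to change.** Reconcile Sections 4.2B and 7.2 so that one stated rule covers a TRF at any time from the end of the first course to the first trial infusion. It should include the short stretch between randomisation and that infusion, and say whether the patient may be randomised or, if already randomised, start trial medication. The content of the rule is a clinical decision for the sponsor.

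For the secondary endpoint in Section 7.1.2, count only TRFs whose worsening begins after randomisation, and record earlier ones as a baseline feature. Align the footnote in Section 2 with that wording.

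The cost is a sentence or two in Sections 4.2B and 7.2, one in the endpoint definition, and the date on which worsening began on the case report form if it is not already collected. Sample size and primary analysis do not change.

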### **4.3. Exclusion criteria**

#### **A. To enter this GBS study**

- Age less than 6 years.
- Patient known to have a severe allergic reaction to properly matched blood products or plasma products.
- Pregnancy or breastfeeding.
- Patient known to have a selective IgA deficiency.
- Patient shows clear clinical evidence of a polyneuropathy caused by e.g. diabetes mellitus (except mild sensory), alcoholism, severe vitamin deficiency, porphyria.

- Patient received immunosuppressive treatment (e.g. azathioprine, cyclosporine, mycophenolatmofetil, tacrolimus, sirolimus or > 20 mg prednisolon daily) during the last month.
- Patient known to have a severe concurrent disease, like malignancy, severe cardiovascular disease, AIDS, severe CARA.
- Inability to attend follow-up during 6 months.

#### **B. Relative contra-indications for second IVIg dose:**

- Patients known to have severe kidney dysfunction (GFR below 40 ml/min).
- Pre-existing risk factors of thrombo-embolic complications or severe ischemic heart disease.

These patient groups run a greater risk (although they are still rare) to develop serious complications like acute tubular necrosis and thrombo-embolic events. To prevent this they should be pre-treated with fluids and infusion rate of the trial medication must be adjusted.

### **4.4. Sample size calculation**

- We will select patients with poorest prognosis (mEGOS 6-12), this corresponds with approximately 50% of the population.
- Calculations showed that the prognosis of this group (mEGOS 6-12) is poor both at 4 weeks (85% unable to walk unaided) and at 26 weeks (35% unable to walk unaided).
- We presume that a second dose of IVIg in patients with poor prognosis (mEGOS 6-12) will raise the percentage of patients improving on the GBS disability score at 4 weeks with 15-25%. For power analysis for our primary outcome we used an improvement of 20%.
- Assuming a 20% improvement in unadjusted data and with a dichotomous outcome (being able to walk unaided versus being unable to walk unaided) we will need ( $\alpha=0.05$  and power=0.80) 290 patients in total (145 poor and 145 good prognosis).
- The power increase through covariate adjustment and the use of the ordinal outcome may be expected to result in a reduction in required sample size of 40 to 50% [31]. This leads to a required sample size of 60% of 290 patients = 174 patients.
- Based on previous calculations 50% of 174 patients (n=87) will have a poor prognosis. This group of 87 patients will be randomized to receive a second course of IVIg (n=44) or placebo (n=44).
- We expect that a sample size of 174 patients is well feasible with approximately 3 years of accrual.

